- In addition to the difference in surgical method, the two groups will be compared by recording the variables for radiology and clinical surgical outcomes while receiving the identical treatments and follow-up (day of surgery as well as 2 weeks, 3 months, 6 months and 1 year after the surgery). The patients planned to be enrolled in this study will be given an explanation on the objectives and method of the study from the study coordinators before participating, and become enrolled in the study by signing the informed consent form. Screening assignment numbers are assigned as a 6-digit number – the first digit of the randomization number represents the clinical trial site; the second digit represents the sub-study; the third digit represents S in Screening; and the last three digits represent the serial number for enrollment (e.g. B1S-001 -> first screened patient for detailed surgery 1 at Seoul National University Bundang Hospital)

- Among subjects who have agreed to participate in the study voluntarily and have signed the informed consent form, those who meet the inclusion and the exclusion criteria will be randomized to one of the two groups in 1:1 ratio.
- For randomization, the permuted block randomization method will be used. Randomization will be applied to subjects in sequential order starting from Subject no. 1 using iCReaT, a web-based eCRF. The investigator will perform the corresponding surgery depending on the randomization result for each subject. To minimize bias, randomization will be performed by a researcher and the randomization code will be notified to the surgeon immediately prior to the surgery.
- The randomization number is assigned as a series of 5-digit number in which the first digit represents the clinical trial site; the second digit represents the sub-study; and the remaining 3 digits represent the serial number for enrollment (e.g. B1-001 -> first enrolled patient for detailed surgery 1 at Seoul National University Bundang Hospital)
- All basic tests and questionnaires will be conducted at prior to surgery, on the day of surgery as well as at follow-up 2 weeks, 3 months, 6 months and 1 year after the surgery.

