# Patients with lumbar spinal stenosis who will undergo uniportal endoscopic decompressive laminectomy

- Target sample size: 120 subjects (Study group: 60 subjects, Control group: 60 subjects, including 20 % drop-out rate)
- Primary outcome: ODI (Oswestry disability index)
- According to a previous study [1], the MCID (Minimal clinical important difference) of ODI was 12.8 and in another previous study [3], the standard deviation of the ODI value at 1 year after decompressive laminectomy was 18.8. Assuming an equivalence limit of 12.8, under the conditions of alpha = 0.05, power = 0.90, two-sided 95% confidence interval, and follow-up loss at 20%, 60 participants are needed in each group.

[figure not shown]

Subject Recruitment Plan

This is a prospective, multicenter study which will recruit subjects at the Department of Neurosurgery of Seoul St. Mary’s Hospital, Chundam Woorideul Spine Hospital and the Wiltse Memorial Hospital (Anyang). Those who are planning to undergo one-segment or two-segment decompression surgery for lumbar spinal stenosis will be recruited as subjects and advertisement for subject recruitment will not be used.

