Statistical analysis method: Equivalency will be declared if the upper and lower limits of the 95% confidence interval (CI) of the treatment difference value of each group’s ODI score at 12 months postoperatively fall within the pre-defined equivalence margin (+-12.8).

1. Secondary Endpoints

The secondary endpoints for this trial include clinical outcomes (VAS, EQ5D-5L, ODI, walking distance and time, satisfaction after surgery, time required to return to daily activities postoperatively, POSAS), radiographic outcomes, and other surgery-related outcomes.

Statistical analysis method: For each group, the differences from the baseline values to the postoperative values and differences in the pattern of change between the two groups are analyzed using repeated measures analysis of variance (ANOVA). In addition, for specific within-group or between-group comparisons at each time point, the t-test is used, while applying the adjusted significance level considering the multiplicity of the test.

Satisfaction after surgery, time required to return to daily activities postoperatively, Patient and Observer Scar Assessment Scale(POSAS scale)

Statistical analysis method: The satisfaction after surgery, the time to return to daily activities postoperatively, and POSAS scale score at the time of final postoperative follow-up are comparatively analyzed between the two groups using the t-test.

- Radiographic outcomes

Examination of the occurrence of complications during the final follow-up using simple radiographs (Development of spondylolisthesis, progression of degenerative lumbar spinal conditions, etc.), analysis of surgical outcomes through postoperative MRI (or CT)

- Statistical analysis method: The occurrence of complications is examined for each group, and Chi- square test or t-test is used for comparative analysis on the difference between the two groups for the degree of central canal release and the canal dimension measured using postoperative MRI or CT.

- Other surgery-related outcomes

Comparison between the two groups on other surgery-related outcomes. [size of the surgical skin incision, postoperative drainage, operative time, duration of hospitalization (hours), Postoperative (From immediately after surgery to discharge from the hospital), postoperative Day 1 creatine kinase (CK, CPK)]

Statistical analysis method: The degree of difference between the two groups is evaluated using the chi-square test or t-test.

General Statistical Analysis

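### The named two-group tests for a three-hospital trial leave out site, and no site term is stated for the primary interval; adding one is a modest, nearly free gain in efficiency

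*Protocol*

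**What the plan says.** **Sites.** The objectives refer to three study sites, and the Subject Recruitment Plan names three hospitals.

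**Allocation.** Study design, and the later section on the control group and randomization method, specify 1:1 permuted blocks applied in sequence from subject number 1 through a web-based eCRF. No stratification factor is named. On the randomization number, Study design says that "the first digit represents the clinical trial site; the second digit represents the sub-study; and the remaining 3 digits represent the serial number for enrollment". Its example, B1-001, is explained as the first enrolled patient at one particular hospital.

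**Secondary analyses.** For incision size, drainage, operative time, hours in hospital and day-1 creatine kinase, "The degree of difference between the two groups is evaluated using the chi-square test or t-test". Satisfaction, return to daily activities and the scar score are compared by t-test. Canal release and canal dimension are compared by chi-square test or t-test. Repeated outcomes are analysed by repeated measures ANOVA, with t-tests at single time points. Site appears in none of these.

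**Primary analysis.** Equivalence is declared if the "95% confidence interval (CI) of the treatment difference value of each group’s ODI score at 12 months postoperatively" lies within ±12.8. No model is named, and the interval is called neither adjusted nor unadjusted.

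**The concern.** When allocation is balanced within hospitals, differences between hospitals cancel out of the comparison of arms. A two-sample test does not know this. It leaves the between-hospital variance in its error term, so its standard error exceeds the true one. The test then rejects less often than its nominal level, and the interval is wider than it needs to be.

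Even without blocking by site, leaving out a prognostic factor gives away precision. Hospitals are likely to differ in surgeons, discharge practice and drain use, so the outcomes for which the protocol names the simplest tests are those on which site is most likely to matter. At stake is power for those comparisons and, to a smaller degree, for the equivalence verdict on ODI.

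**Working it through.** **Inputs from the protocol (Statistical Consideration).** Margin: "Assuming an equivalence limit of 12.8". SD: "the standard deviation of the ODI value at 1 year after decompressive laminectomy was 18.8". Error rates: "under the conditions of alpha = 0.05, power = 0.90", with a two-sided 95% interval. Dropout is 20%, with 60 per group, so 60 × 0.80 = 48 evaluable per group.

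**Assumptions, not in the protocol.** True difference 0; three equal sites; additive site effects; a share r of the total variance lying between sites, shown over a range.

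**The plan's own figure.** For two one-sided tests, n = 2 × [SD × (z for alpha + z for 1 − β/2) / margin]².
- With 0.05 per side: 2 × [18.8 × (1.645 + 1.645) / 12.8]² = 46.7, so 47, and 47/0.80 gives 59. Taking 48 gives exactly 60. The stated 60 is reproduced to within one patient.
- With 0.025 per side, which is what a 95% interval implies: 56.07, so 57, and 57/0.80 gives 72. This does not reproduce 60. It is a separate matter, but it explains why the power figures below start near 83% and not at 90%.

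The plan uses one total SD with no site component.

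**Effect of leaving out site when blocks run within site.** SE = 18.8 × √(2/48) = 3.84. With balance within site, the true SE of the difference is 3.84 × √(1 − r), while the two-sample test goes on using about 3.84.
- True error of a nominal two-sided 5% test: 2 × [1 − Φ(1.96/√(1 − r))].
- Equivalence power, unadjusted: 2Φ[(12.8 − 1.96 × 3.84)/(3.84√(1 − r))] − 1.
- Equivalence power, adjusted: 2Φ[12.8/(3.84√(1 − r)) − 1.96] − 1.

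| Site share r | True error of 5% test | Power, unadjusted | Power, site-adjusted | Gain (points) |
|---|---|---|---|---|
| 0 | 5.0% | 83.1% | 83.1% | 0 |
| 5% | 4.4% | 84.2% | 85.6% | 1.4 |
| 10% | 3.9% | 85.3% | 88.0% | 2.7 |

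**Check by simulation.** With 20,000 trials, 16 patients per arm in each of three sites, t-based intervals and an additive linear model, power without and with site is 82.4% and 82.4% at r = 0, 83.2% and 84.6% at 5%, and 84.3% and 87.2% at 10%. The gains are 0, 1.4 and 2.9 points. Coverage of the unadjusted 95% interval is 95.5% at 5% and 96.0% at 10%. The formulas run about one point high in power because they use normal quantiles, but the gains agree.

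**Without blocking by site.** At r = 10%, a further simulation gives 82.2% unadjusted and 86.3% adjusted. Adjustment helps here too, but the unadjusted test keeps about its nominal error, so the conservatism disappears.

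**Operative outcomes.** The protocol gives no effect sizes or power for these. As an illustration only, take a superiority test with 80% power by the usual formula (noncentrality 2.80) and a site share of 30%. Its actual power would be about 84% unadjusted and 92% adjusted. The 30% has no basis in the protocol; it shows what a strong site effect would do.

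**The case against.** The strongest reply is that the protocol never says allocation is stratified by site. A reader might infer from the numbering that blocks are site-specific and the arms balanced within site by design. The text does not support that as a fact. A site prefix and a serial are a labelling rule, compatible with separate lists but not proof of them, and the hospital in the example is not among the three in the Subject Recruitment Plan. This objection stands. The claim of conservatism is therefore conditional.

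A reader might also take the primary interval to be unadjusted. The protocol gives a decision rule and no model, and a statistical analysis plan could supply the covariates. All that can be said is that no site term is stated.

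A third tempting reading is that the trial loses power against its plan or that its inference is invalid. Neither follows. The sample size rests on a total SD, and unadjusted power rises slightly with the site share; what is forgone is the gain from a better analysis. Under additive site effects the Type I error is not inflated and false equivalence is not made easier. For incision size, which differs by design (about 1 cm against about 3 cm), power is hardly an issue.

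Finally, the calculation assumes balance within site that survives dropout, and no site-by-treatment variation. Such variation could push the standard error the other way.

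What the objection does not remove is that the t-tests and chi-square tests for secondary and operative outcomes are named in the protocol, in a three-hospital trial, with site absent.

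**Conclusion.** The point holds as one of efficiency. If site is prognostic, the named secondary tests are less efficient than site-adjusted ones, whether or not allocation is blocked by site. If it is blocked by site, they are also conservative, with a true error of about 4.4% at a 5% site share and 3.9% at 10%.

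For the primary equivalence test the forgone power is modest: none at a share of 0, about 1.4 points at 5% and about 3 points at 10%, given within-site balance, additive site effects, SD 18.8, 48 evaluable per group and a true difference of 0. The site share is an assumption throughout. The gain may be larger for hospital stay, drainage and operative time, but the protocol gives no figures from which to size it.

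**What to change.** 1. In Study design and in the section on the randomization method, state whether permuted blocks are generated within site.
2. Under the primary endpoint, estimate the 12-month ODI difference and its 95% confidence interval from a linear model with treatment and site as fixed effects.
3. Use the same model in place of the two-sample t-tests for continuous secondary and operative outcomes, and a Cochran-Mantel-Haenszel test stratified by site in place of the chi-square tests for categorical outcomes.
4. Keep the unadjusted tests as sensitivity analyses.

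The cost is a change of wording and two degrees of freedom (92 in place of 94 residual with 96 evaluable patients). No new data are needed, since site is already part of the subject number. If sites turn out not to differ and blocks were not within site, adjustment would cost a little precision through chance imbalance.

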The surgical method investigated in this study is the most commonly used technique for lumbar spinal stenosis, and the clinical study is conducted through pre- and post-operative surveys and analysis of clinical and imaging data, so there is no harm to the subjects. However, if the subject refuses to participate in the study, the trial will not proceed with the subject. In addition, although this study is conducted on a patient group, there is no obligation or undue influence for participation, and there is no disadvantage to the patient for not participating in the study. Among those who voluntarily agreed to participate in this study and signed an informed consent form (ICF), those who met the inclusion criteria for this study and were not applicable to the exclusion criteria were selected, and subjects were randomly assigned to either of the study or control groups. The Principal Investigator (PI) of this study will not exclude subjects who are likely to participate in this study based solely on race or socioeconomic status. As long as the subject is eligible in terms of inclusion/exclusion criteria, the PI will make every effort to encourage the subjects to participate in the study, and inform the subjects of the objectives of this study so that they can properly represent the total of the patients who will undergo the treatment.

Assessment and Analysis of Study Results and Items for Observation

- **Demographic information:** Age, gender, and date of surgery of subjects

– **Physical examination and basic tests:** Medical history, smoking habits, basic blood tests, physical examination

– **Radiological tests:** The subjects undergo simple radiography and MRI (or CT) examination for baseline assessment. After surgery, during the hospitalization period, the degree of canal release, complications, and recurrence are examined through simple radiography and MRI (or CT) scans.

- **Oswestry disability index (ODI) questionnaire:** Scoring of the Oswestry disability index (10 items) is conducted at the visit. The investigator hands out the subject a questionnaire, and asks the subject to rate each item on a five-point scale for self-report. The rated score is expressed as a percentage of the total score of the answered questions excluding the questions not completed by the subject.

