- **EQ5D-5L questionnaire:** The EQ5D-5L questionnaire (5 items) is conducted at the visit. The investigator hands out the subject a questionnaire and asks the subjects to rate and indicate each item for self-report. The total score of the indicated items is converted using the EQ5D value set for calculation.

- **VAS score ( pain scale):** The degree of pain felt by the subject during activity is assessed using a 100mm VAS (Visual Analogue Scale) for both lower back and the legs. The investigator explains the VAS to the subject and asks the subject to rate each item and indicate accordingly for self-report. In addition, the degree of pain in the surgical site (Postoperative Day 1 or Day 2) is also investigated using VAS.
- **Walking time:** The changes in values in the questions on walking ​​at postoperative 2, 12, 24, and 52 weeks are compared to the baseline values.
- **Satisfaction after surgery:** At the 1-year follow-up visit, the investigator hands out the questionnaire to the subject and asks the subjects to indicate for self-report.
- **Return to daily activities after surgery:** The time required to return to daily activities postoperatively (week)
- **Scar after surgery (POSAS[Patient and Observer Scar Assessment Scale] patient scale 2.0):** The patient assesses the postoperative scarring with 6 items and scored on a ten-point system, with a score of 1 indicative of normal skin and a score of 10 indicative of the worst scar imaginable, and the total score of the assessment is 60.

- **Other surgery-related outcomes:** The size of the surgical skin incision, postoperative drainage, operative time, duration of hospitalization (hours), postoperative Day 1 creatine kinase (CK, CPK) are also evaluated.

- **Presence of adverse events and complications:** Adverse events requiring revision surgery related to the intervention. When a patient arrives at the ward after completing the surgery, a resident (or fellow, clinical instructor, nurse, investigator, etc.) who is blinded to the surgical method examines the patient to determine whether there are any complications related to the intervention or any serious complications that require revision surgery.

Efficacy Assessment Criteria, Assessment Method, Interpretation

1. Primary Endpoint

The primary endpoint of this trial is the difference between the ODI score measured at baseline and that measured 12 months postoperatively.

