General principles of analysis

- For continuous variables, descriptive statistics (number of subjects, mean, standard deviation, median, minimum, maximum) are presented, and for categorical variables, frequency (N) and percentage (%) are presented.

- In the analysis of the primary efficacy endpoint, if missing data occurs due to dropout, etc., the data are processed as a failure and the non-responder imputation (NRI) method is used.

- If the clinical trial is discontinued according to the discontinuation criteria, the data are handled as missing values.

- In the analysis of secondary efficacy endpoints, when there are missing values in the data, a method of last observation carried forward (LOCF) is used.

- For the analysis of the safety set, when there are missing values in the data, the data shall be analyzed as it is without performing imputation for the missing values (OC method).

Handling of analysis sets

- The analysis sets are categorized into safety set, full analysis set (FAS) and per protocol (PP) set.

- Efficacy data are analyzed using both FAS and PP, and final determination on efficacy endpoints is conducted by FAS analysis based on the modified ITT (intention to treat).

- Data on safety are analyzed for the safety sets.

- For the analysis of efficacy endpoints, when there are missing values in the data, the data shall be analyzed as it is without performing imputation for the missing values.

Definition of analysis sets

• FAS (Full Analysis Set): Subjects who met the inclusion/exclusion criteria and who underwent randomization to receive the intervention at least once during the trial period are included in FAS. In the efficacy analysis, regardless of the actual status of undergoing the surgery, analysis is performed based on the treatment group assigned by randomization.

• PP (Per Protocol Set): Subjects who have completed the trial without major protocol violations among the full analysis set (FAS) are included in PP set. However, if the trial is discontinued according to the discontinuation criteria, the clinical trial is considered to be completed and included in the PP analysis. For items of major protocol violations, see Section 13-5.

• Safety Set: Subjects who were randomized and have undergone the surgery at least once during the trial period are included in the safety set. In the safety analysis, analysis is performed based on the classification according to the actual type of surgery received.

|  | | | | | | |

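### The protocol gives two conflicting missing-data rules for the primary ODI analysis, and the non-responder rule cannot be run as written because no failure value is defined

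*Protocol*

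**What the plan says.** Under General principles of analysis, the protocol says of primary-endpoint data missing through dropout or similar causes that "the data are processed as a failure and the non-responder imputation (NRI) method is used". The same list prescribes LOCF for secondary efficacy endpoints.

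Under Handling of analysis sets it adds: "For the analysis of efficacy endpoints, when there are missing values in the data, the data shall be analyzed as it is", and the sentence goes on to rule out imputation. It is not limited to secondary endpoints or to the per-protocol set. It follows the statement that efficacy is decided on the FAS.

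The endpoint is continuous: "The primary endpoint of this trial is the difference between the ODI score measured at baseline and that measured 12 months postoperatively". On scoring, "The rated score is expressed as a percentage of the total score of the answered questions". Equivalence is declared when both limits of the 95% CI for the treatment difference lie within ±12.8. Under Statistical Consideration the sample size assumes that "the standard deviation of the ODI value at 1 year after decompressive laminectomy was 18.8", with "alpha = 0.05, power = 0.90, two-sided 95% confidence interval, and follow-up loss at 20%, 60 participants are needed in each group".

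**The concern.** The primary endpoint is an efficacy endpoint, so both sentences apply to it and they give opposite instructions. The protocol states no order of precedence.

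Non-responder imputation needs either a binary responder outcome or a stated score for a failure. The protocol has neither, so an analyst would have to choose one; returning the patient to baseline and assigning the worst score are the obvious candidates.

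The choice matters more than usual in an equivalence trial. Giving missing patients in both arms the same value pulls together arms that truly differ, which favours the claim. A worst-score value inflates the variance and works against the claim. Unequal dropout can create a difference between arms that do not differ. The plan allows for 20% loss, so the number of patients affected is not trivial.

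**Working it through.** **Inputs from the protocol.** 60 per arm, SD 18.8, margin 12.8, two-sided 95% CI, 20% loss.

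**Assumed, because the protocol gives no means.** Better-arm improvement 20–40 points; 12-month mean ODI 20–40; missing rates of 10% and 20%. The SD of 18.8 is that of the 1-year score and is applied here to change as well.

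**The plan's own figure.** For two one-sided tests, n = 2 × [SD × (z₁₋ₐ + z₁₋β/₂) / margin]².

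- At 5% per side: 2 × [18.8 × (1.645 + 1.645) / 12.8]² = 46.7, so 47 (48 with the t distribution). Dividing by 0.8 gives 59 (60). The stated 60 is reproduced.
- At 2.5% per side, which is the stated 95% CI rule: 2 × [18.8 × 3.605 / 12.8]² = 56.1, so 57, or 72 after inflation. That is a separate matter. It explains why the benchmark below is about 82% and not 90%.

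**Benchmark: no imputation.**

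- 48 per arm: SE = 18.8 × √(2/48) = 3.84; half-width 1.986 × 3.84 = 7.62; chance of declaring equivalence with identical arms = 2Φ[(12.8 − 7.62)/3.84] − 1 ≈ 0.82.
- 54 per arm: SE = 3.62; half-width 7.17; 2Φ[(12.8 − 7.17)/3.62] − 1 ≈ 0.88.
- At a true difference of 12.8, false equivalence is about 2.5%.

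**Failure = no change from baseline.** A proportion p in each arm is set to 0, so the true difference shrinks to (1 − p) × 12.8, which is 10.24 at 20% and 11.52 at 10%. Each arm's variance becomes (1 − p) × 18.8² + p(1 − p) × mean². For improvements of 30 and 17.2 at 20% missing:

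- Variances: 282.8 + 144.0 = 426.8 and 282.8 + 47.3 = 330.1; pooled SD 19.45; SE = 19.45 × √(2/60) = 3.55; half-width 7.03.
- False equivalence ≈ Φ[(12.8 − 7.03 − 10.24)/3.55] = Φ(−1.26) ≈ 0.10. Simulation gives 0.107.

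**Failure = ODI 100, identical arms, 20% missing.**

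- Mean ODI 20: variance 282.8 + 0.16 × 80² = 1306.8; SD 36.1; SE 6.60; half-width 13.1. The typical half-width exceeds the margin. Simulation gives about 2%.
- Mean ODI 40: variance 282.8 + 0.16 × 60² = 858.8; SD 29.3; SE 5.35; half-width 10.6; 2Φ(0.41) − 1 ≈ 0.32.

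**Results, each patient missing at random:**

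| Quantity | Rule | 10% missing | 20% missing |
|---|---|---|---|
| False equivalence, true difference 12.8 | No imputation | about 2.5% | about 2.5% |
| | Failure = no change (improvement 20–40) | 5–6% | 9–12% |
| Equivalence declared, identical arms | No imputation | about 88% | about 82% |
| | Failure = ODI 100 (mean ODI 20 to 40) | 29% to 57% | 2% to 32% |

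If exactly 12 per arm are missing, false equivalence under no change runs from 10.9% down to 4.4% for improvements of 20 to 40. The ODI 100 figure is then 0.6% at mean ODI 20 and about 52% at mean ODI 40.

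**Unequal dropout, 10% against 30%, failure = no change, identical arms.** The spurious difference is (0.30 − 0.10) × mean improvement, or 3 to 7 points for improvements of 15 to 35. At 25 points it is 5.0, and equivalence is declared in about 59% of trials, against about 81% without imputation.

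**One data set, two verdicts.** Suppose 18 endoscopic and 6 control patients drop out and completers differ by 4 points.

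- No imputation: 4 ± 1.986 × 18.8 × √(1/42 + 1/54) = −3.7 to 11.7, equivalent.
- Dropouts imputed around 20 points above the control completers' mean, with SD 18.8: difference 0.7 × 4 + 0.3 × 20 − 0.1 × 20 = 6.8; variances 353.4 + 0.21 × 16² = 407.2 and 353.4 + 0.09 × 20² = 389.4; SE = √(796.6/60) = 3.64; CI −0.4 to 14.0, not equivalent.

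**The case against.** The best defence is that the specific rule overrides the general one: the primary endpoint has its own rule, the secondary endpoints have theirs, and the no-imputation sentence is only a general remark. This is a partial answer. The protocol does not say so, and the rule that would survive is the one without a failure value. A numeric value could be left to an SAP that is not at hand, but that would not remove the conflict between two stated rules.

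Several stronger readings are tempting and are not supported:

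- *Non-responder imputation can never be used with a continuous score.* It can, once a value is assigned, as the calculations above do. It cannot be run from this text.
- *The verdict always turns on the rule.* With identical arms, 20% dropout in each and a failure value 10–30 points above the completers' mean, the two rules disagree in only about 11–12% of simulated trials. Large disagreement needs unequal dropout or a worst-score value.
- *Equivalence becomes unreachable.* That is approached only in the corner of ODI 100, a low mean ODI and the full 20% missing.
- *The 20% inflation shows that no imputation was intended.* A sponsor may inflate under either rule.
- *The choice will be made after unblinding.* The protocol leaves this open, but an SAP may settle it.

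**Conclusion.** The rule is wrong as written. Two incompatible instructions govern the primary analysis, and one of them lacks the definition needed to carry it out. This is not detail deferred to an SAP, because the protocol states both rules.

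The consequence can be material in either direction: false equivalence up to about four to five times its 2.5% benchmark at the planned 20% loss, or a large fall in the chance of declaring truly identical arms equivalent. The sizes rest on means that the protocol does not give, on the 1-year SD standing in for the SD of change, and on the missing rate. They should be read as ranges. The contradiction itself rests on no assumption.

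**What to change.** Delete the non-responder sentence for the primary endpoint and fix a single rule before unblinding. A suitable choice, though not the only one, is a likelihood-based mixed model on the ODI visits already scheduled at 2, 12, 24 and 52 weeks, with baseline ODI. The 52-week contrast and its 95% CI would be compared with ±12.8, without single-value imputation. Add one delta-adjusted sensitivity analysis in which missing patients are made progressively worse.

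Also reconcile the general no-imputation sentence with the LOCF rule. Both now apply to the secondary endpoints, which again include ODI, and deleting the non-responder sentence alone would leave that conflict in place.

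The cost is protocol wording and a little more analysis work. No further patients, visits or data are needed for this change.
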